## Abstract

**Background:**

This protocol concerns the assessment of cost-effectiveness of hospital health information technology (HIT) in four hospitals. Two of these hospitals are acquiring ePrescribing systems incorporating extensive decision support, while the other two will implement systems incorporating more basic clinical algorithms. Implementation of an ePrescribing system will have diffuse effects over myriad clinical processes, so the protocol has to deal with a large amount of information collected at various ‘levels’ across the system.

**Methods/Design:**

The method we propose is use of Bayesian ideas as a philosophical guide.

Assessment of cost-effectiveness requires a number of parameters in order to measure incremental cost utility or benefit – the effectiveness of the intervention in reducing frequency of preventable adverse events; utilities for these adverse events; costs of HIT systems; and cost consequences of adverse events averted. There is no single end-point that adequately and unproblematically captures the effectiveness of the intervention; we therefore plan to observe changes in error rates and adverse events in four error categories (death, permanent disability, moderate disability, minimal effect). For each category we will elicit and pool subjective probability densities from experts for reductions in adverse events, resulting from deployment of the intervention in a hospital with extensive decision support. The experts will have been briefed with quantitative and qualitative data from the study and external data sources prior to elicitation. Following this, there will be a process of deliberative dialogues so that experts can “re-calibrate” their subjective probability estimates. The consolidated densities assembled from the repeat elicitation exercise will then be used to populate a health economic model, along with salient utilities. The credible limits from these densities can define thresholds for sensitivity analyses.

**Discussion:**

The protocol we present here was designed for evaluation of ePrescribing systems. However, the methodology we propose could be used whenever research cannot provide a direct and unbiased measure of comparative effectiveness.

## Background

### Provenance

This protocol concerns the assessment of cost-effectiveness of hospital health information technology (HIT). The cost-effectiveness analysis forms part of a National Institute for Health Research (NIHR) funded research programme to evaluate the implementation, adoption, effectiveness and cost-effectiveness of ePrescribing systems as they are introduced into a sample of hospitals in England (RP-PG-1209-10099). Four hospitals will be studied – before, during, and after implementation of an ePrescribing system, as described in the application for funding (RP-PG-1209-10099) [1-4]. Two hospitals are acquiring systems with extensive decision support, while the other two will implement systems incorporating only the most basic clinical algorithms. Three types of data will be collected from each site:

1. Qualitative data on the acceptability and adoption of the system;

2. Quantitative data on prescribing safety;

3. Cost data.

In this paper, we describe the protocol for the cost-effectiveness analysis that will follow data collection. For reasons that have been described in a previous paper [5], cost-effectiveness analysis of large scale service delivery interventions raises issues that are not part of standard Health Technology Assessment (HTA). We now describe some of these issues in more detail.

### Issues in evaluation of large scale service changes

#### Diffuse impact of generic health information technology interventions

Implementation of an ePrescribing *system* is an example of a generic intervention with diffuse effects, spanning out over myriad clinical processes [5], in contrast with more targeted interventions focussed on a limited number of end-points. This crucial distinction is represented diagrammatically in Figure 1. Some applications of HIT have narrow focus – mobile phone-based decision support to improve compliance with asthma treatment, for example [6] – and can be considered as examples of targeted service interventions. On the other hand, a comprehensive ePrescribing *system* has many of the features of a generic service intervention. It has a potential impact on work patterns (at the system level) and it may affect a large number of clinical processes (e.g. prescriptions) and contingent outcomes (e.g. preventable adverse events) at the clinical level. It is important to note that each adverse event may be affected to a different degree by the intervention and will be associated with a particular utility. This is in contrast to typical HTA, which may have an effect on one, or a limited number of, outcomes. The protocol thus has to deal with a large amount of information collected at the system, clinical process and outcome ‘levels’.

**Figure 1 F1:**
[figure not shown]
**Representation of the widespread effects of a generic intervention.** *First as intended and then as actually implemented. †Sometimes referred to as organisation level outcomes to include morale, staff attitude, knowledge, effect on patient flows etc.

#### Lack of contemporaneous controls

This study, in keeping with many in the service delivery/quality improvement literature, is based on a before and after design. A preferable controlled before and after design [7] (or randomised comparison) was not possible within the funding envelope. The study therefore cannot control for general temporal trends and is also subject to selection effects given the non-experimental design. The protocol thus needs to find a way to accommodate the possibility of bias in estimates of parameters used to populate the health economic model.

#### Integrating study results with evidence external to the index study

Given the above uncertainties, decision makers will want to ensure that parameters used in the estimation of cost-effectiveness take account of evidence from the large literature on HIT systems [8,9]. This cannot be achieved by standard meta-analysis given the highly variegated nature of the salient literature.

### Confronting the issues – epistemology of large-scale service changes

Elsewhere we have suggested that generic service, and many policy, interventions cannot be evaluated solely by direct parameter estimates that have been so successful for the evaluation of clinical treatments and for targeted service interventions [10]. The framework outlined above provides a way forward in circumstances where ‘knock-down’ evidence is elusive. It provides a ‘half-way house’ between fruitless striving for a clear cut quantitative ‘answer’ and reverting to a completely unquantified ‘interpretivist’ [11] or even ‘realist’ approach. We propose use of Bayesian ideas as a philosophical guide (as proposed by Howson and Urbach) [12] rather than a mathematical method to update a prior probability density. This issue is explored further in the discussion.

The scientific method can thus be conceptualised as the process by which data are collected and analysed so as to inform a degree of belief concerning the parameter(s) of interest [13]. The data concerned may be of various types. These diverse data types are assembled to inform a probabilistic judgment.

The intellectual model we propose has the following features:

1. Its epistemology is Bayesian, treating probability as a degree of belief.

2. Quantitative study data are not used as direct parameter estimates for use in models, but as information to inform subjective estimates of effectiveness.

3. Qualitative study data will also contribute to the subjective estimates of effectiveness.

4. Subjective probability densities will be elicited from groups of experts exposed to the above quantitative and qualitative data, and also data from studies external to the index study.

5. The densities will be pooled across experts for use in health economic models (both for the base case and to describe thresholds for sensitivity analyses).

In summary, we will assemble both quantitative and qualitative data, from different sources, to triangulate any evidence of effectiveness or lack of effectiveness, and establish parameters that summarise evidence of effectiveness [10].

## Methods/Design

### Overview of cost-effectiveness model

Evaluation of cost-effectiveness will proceed as follows [14]:

1. Evaluate effectiveness in reducing the frequency of preventable adverse events;

2. Assign utilities for these adverse events;

3. Calculation of expected health benefit;

4. Determine costs (fixed and recurrent) of procuring, implementing, operating and maintaining HIT systems and model the cost consequences of adverse events averted;

5. Calculation of cost-effectiveness.

The first two quantities (effectiveness in reducing adverse events, and utilities) are used to calculate health benefit (assuming that this cannot be captured directly through a quality of life measurement – see below). Component 4 allows *net* costs to be estimated. Costs and benefits can then be consolidated in a measure of incremental cost utility or cost benefit. An overall framework for our proposed evaluation is given in Figure 2. The perspective of the evaluation is that of the health services, at least in the first instance – a point to which we return.

**Figure 2 F2:**
[figure not shown]
Framework for the evaluation.

### Evaluation of effectiveness

#### Consideration of quantitative end-points

There are four (non-exclusive) end-points that may be used in measurement relating to effectiveness:

1. Generic quality of life;

2. Adverse event rates (including mortality);

3. Error rates;

4. Triggers (for errors or adverse events).

None of the above end-points are unproblematic. We now discuss each to determine which are more suitable in the context of this study.

##### Generic quality of life

A generic measurement of quality of life, using a measurement tool such as the SF36 [15], is an attractive option because such a measurement (when combined with death) consolidates all the various adverse events that the intervention is designed to prevent. This end-point thus gets around the problem that each adverse event has its own utility and may be affected differentially by the intervention. The problem, however, is that prescribing errors make only a very small contribution to generic quality of life since less than 1% of patients suffer a preventable medication-related adverse event during a single hospital stay and the majority, as we shall see later, are minor and short-lived [16]. In short, any ‘signal’ would be lost in ‘noise’; a false null result would be likely even if worthwhile improvement had occurred.

##### Prescribing error rates

Prescribing errors are much more common than error-related (i.e. avoidable) adverse events; the baseline error rate is about 5% [18], and hypothesised reductions in these errors of 30% (two percentage points) or more are in line with those found in the literature [8,9]. This end-point therefore yields more manageable sample size requirements (Table 2). Samples sufficient to detect a 30% improvement with 80% power are feasible under the funding envelope of the study. However, this end-point is far from perfect because:

**Table 2 T2:** Sample size calculations for detection of reductions in error rate

**Risk ratio**	**Power (%)**	**Sample size (total)**
0.6	80	3,210
0.7	80	5,940*
0.8	80	13,888
0.6	90	4,230
0.7	90	7,862
0.8	90	18,456

*Similar to proposed sample in this study.

Sample size calculations for detection of reductions in error rate; baseline error rate 5% and other assumptions, as in Table 1.

1. Errors are surrogates for adverse events. It is therefore necessary, in any cost-effectiveness analysis, to infer adverse event rates from error rates – a step that introduces further uncertainty.

2. Error rates are associated with considerable measurement error [19], and detection can be affected by learning effects, fatigue [20], and conceivably also by use of a computer.

3. The more serious an error, the less likely it is to be perpetrated [21], and so a study based on a limited sample is likely to underestimate effects of an intervention on rare, but egregious, errors.

##### Trigger tool methods

Triggers are based on evidence suggesting that a preventable adverse event might have occurred (e.g. administration of vitamin K or anti-narcotics to reverse a putative overdose of warfarin or morphine respectively). The triggers are selected on the basis that they can be easily ascertained from existing data systems – it is easy to search the pharmacy database for use of the above antidotes, for example. Such triggers can be useful in quality improvement programmes where the IT system remains stable over a period where a non IT-based safety intervention is introduced [22]. They are likely to yield a biased result, however, when the IT system is both the intervention of interest and used in collection of end-point data. Furthermore, triggers are not only non-specific, but insensitive [23]. This is because only a small proportion of all medication-related adverse events show up on a trigger tool system.

#### Selection of quantitative end-points

It can be seen from the above analysis that there is no single end-point that adequately and unproblematically captures the effectiveness of the complex intervention that we have been commissioned to study. Following discussion with the programme Steering Group we decided to reject two of the above four possible end-points. Trigger tools were rejected on the grounds that while they are useful in quality control systems within a stable platform, they are likely to be a highly unreliable (biased and imprecise) tool for scientific measurement of the effectiveness of a HIT system. Generic quality of life questionnaires were rejected on the grounds that they could not detect improvement among the small proportion of patients that suffer an avoidable medication-related adverse event.

We will measure error rates and adverse events as the ‘least bad’ options in this study. Error rates will be measured as described in detail elsewhere [24]. In brief, a specified list of 80 errors with potentially serious consequences has been identified by a consensus technique. [25] These errors are reasonably common and by concentrating on a limited number we believe we can identify them with high sensitivity irrespective of the ‘platform’ in use – i.e. irrespective of whether the computer system has been deployed. To mitigate measurement error, observers will be trained, and to reduce the effect of prescribing systems on measurement the reviewers will be on site with access to all prescribing information, whether held on computer or recorded on paper. In this way we plan to make the data collection task as independent as possible from the intervention. We intend to identify errors by examining every prescription within a sample of consecutive patients, as used in many other studies [18].

The observers will also record adverse events that come to light during the study. Each patient case note will be reviewed for adverse events, which will then be examined in detail to determine whether, on the balance of probabilities, they were preventable.

#### Illustrative modelling of adverse events from errors

Errors are important only insofar as they portend adverse events. In order to illustrate the pathway between errors and preventable adverse events, we will model expected reductions in adverse events from (any) reductions in error rates. Since doing so for all 80 errors on the above list would be a laborious and expensive process, we shall do so for exemplars across four error classes – drug interactions, allergy, dose error and contra-indications. Within these classes we have selected errors for which information to populate causal models is available in the literature – a point taken further in the discussion. Further details on this method are given in Additional file 1. Patients are exposed to the risk of error and hence of an adverse event when attending hospital and receiving a prescription. As these are mainly one-off prescriptions, decision trees will be used to model the risk of adverse events. For each of the illustrative errors chosen, the probability of contingent adverse events will be modelled on the basis of information in the literature. Markov chains will be used when one adverse event may lead to another – for example deep venous thrombosis that may lead to pulmonary embolism that, in turn, may lead to death. In this way, we will compute the headroom for reductions in adverse event rates related to certain specific errors, i.e. the reduction in adverse event rates that would be expected if the causal errors could be eliminated. The results will be used to assist expert judgement within the elicitation of subjective probability densities, as described below. Our expectation is that the results of this modelling exercise, with respect to just four errors, will help experts to mentally ‘calibrate’ their subjective probability estimates, with respect to error in general. More specifically, we think that it will mitigate heuristic biases, such as over-confidence and anchoring, itemised by Kadane and Wolfson [26].

#### Classifying adverse events

As stated above, the purpose of the elicitation exercise is to estimate reductions in adverse events. We will have to deal with the fact that there are a very large number of different preventable adverse events. It cannot be assumed that an intervention will affect all events equally. Moreover, each event is associated with its own mean utility. Ascribing a single probability and utility to cover all adverse events is too crude. On the other hand, ascribing a probability and utility to each and every event detected in the study or inferred from errors would be a logistically taxing process and would omit certain rare, but notorious, events such as daily rather than weekly methotrexate administration. Our approach to this problem builds on a previous study by our group, where adverse events were classified according to severity and duration [14]. Classification systems that have been described in the literature are explicated in Table 3.

**Table 3 T3:** Classification systems for adverse events, with prevalence figures (proportion of total adverse events in given category)

**Forster et al. **[27]		**Brennan et al. **[17]		**Hoonhout et al. **[28]		**Yao et al. **[14]	
**Event category**	**Proportion in category**	**Event category**	**Proportion in category**	**Event category**	**Proportion in category**	**Event category**	**Proportion in category**
Death	0	Death	0.136	Death	0.078	Death	0.05
Permanent disability	0.03	Permanent impairment, >50% disability	0.026	Permanent disability	0.047	Permanent impairment, >50% disability	0.02
		Permanent impairment, ≤50% disability	0.039			Permanent impairment, ≤50% disability	0.03
Readmission	0.21	Moderate impairment, recovery >6 months	0.028	Moderate disability	0.617	Moderate impairment, recovery >6 months	0.10
A&E visit	0.11	Moderate impairment, recovery 1–6 months	0.137			Moderate impairment, recovery 1–6 months	0.30
Physician visit	0.14	Minimal impairment, recovery <1 month	0.634	Minimal effect	0.257	Minimal impairment, recovery <1 month	0.50
No extra use of health service	0.51						

We shall use the four category system (i.e. dead, permanent disability, moderate disability, minimal effect) proposed by Hoonhout and colleagues [28]. We have selected this system for two reasons. First, it has the smallest number of categories, and will therefore be the least tedious to implement when probabilities and utilities are elicited. Second, this is the only system for which the costs associated with preventable adverse events in each category are available (Table 4). In subsequent calculations we will make use of the probability of each category of adverse event arising as a result of treatment given in hospital. This is given by the product of the proportions of adverse events in each category (Table 4) and the prevalence of all preventable adverse events (i.e. 0.01 [1%] as referenced above).

**Table 4 T4:** Classification of preventable adverse events that we propose to use in this study*

**State**	**Proportion**	**Utility**	**Mean duration, L (years)**	**Cost, 2009 (€)**	**Comments**	**Example**
Death	0.078	0	3	3,831	Duration here is expected mean survival without the event, as estimated as weighted average from Zegers et al. [29]	Vincristine administered by intrathecal route.
Permanent disability	0.047	To be determined	6	6,649	Costs exclude long-term care. No data on mean duration, but a given adverse event is more likely to be fatal in an older person, so mean survival assumed to be a little longer than life years lost in those who died.	Haemorrhagic stroke in patient prescribed warfarin and macrolide antibiotics.
Moderate disability	0.617	To be determined	0.2	5,973	Duration ≤6 months in 70% of cases (Baker et al. [30])	Pulmonary embolism in large patient given standard (inadequate) dose of heparin.
Minimal effect	0.257	To be determined	0.05	2,979		Transient urticarial rash in known allergic patient given penicillin.

*Based on Hoonhout et al. [28]

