### Calculation of health benefit

When the above data have been collected the health benefit in Quality Adjust Life Years (QALYs) per hospital admission will be calculated as a sum over the four categories of the form:

$$\overset{4}{\underset{i=1}{\sum }}RR_{i}\times p_{i}\times U_{i}\times L_{i}$$

Where for each category (*i* = 1,2,3,4)

*RR*_
*i*
_ is the relative reduction in adverse event rate elicited from the expert group;

*p*_
*i*
_ is the pre-intervention prevalence of the event (i.e. overall prevalence x proportion from table 4);

*U*_
*i*
_ is the estimated loss of utility associated with the event;

*L*_
*i*
_ is the time period (in years) over which the loss of utility is experienced (Table 4).

The above calculation assumes that within the adverse event groupings, change in probability of event occurring, severity of event, and length of adverse event are all assumed to be independent.

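### Table 4 sets permanent disability at 6 years, although its note justifies only slightly more than 3; the 0.2 years for moderate disability is possible but close to the lowest mean its note allows

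*Protocol article*

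**What the plan says.** Under *Calculation of health benefit*, the QALY gain per admission is the sum over four categories of RR × p × U × L, where L "is the time period (in years) over which the loss of utility is experienced (Table 4"). Table 4, under *Classifying adverse events*, supplies L as a fixed number for each category:

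- Death: "Death 0.078 0 3 3,831", so L is 3 years. The comment explains: "Duration here is expected mean survival without the event". These 3 years are therefore the life years lost by those who die.
- Permanent disability: L is 6 years. The comment concedes that no duration data exist and argues that a given event is more often fatal in older people, "so mean survival assumed to be a little longer than life years lost in those who died".
- Moderate disability: "Moderate disability 0.617 To be determined 0.2 5,973", so L is 0.2 years. The comment is "Duration ≤6 months in 70% of cases", with a cited source.
- Minimal effect: "Minimal effect 0.257 To be determined 0.05 2,979", so L is 0.05 years.

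Under *Calculation of cost-effectiveness*, the sensitivity analysis described concerns the effectiveness distribution. *Assigning utilities* adds a possible sensitivity analysis on utilities. Neither mentions L.

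**The concern.** Two of the four durations fit badly with the comments that are meant to support them. For permanent disability the comment is the only basis offered. It leads to a value slightly above 3 years, but the table doubles the 3. For moderate disability, a mean of 0.2 years (2.4 months) looks low when three cases in ten last more than 6 months.

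L is a direct multiplier, so a proportional error in L is the same proportional error in that category's QALYs. The cost-saving formula under *Determining net costs* does not contain L, so a change in L reaches the ICER only through its denominator. Relative reductions are elicited separately by category, so an overstatement in one category cannot be assumed to cancel an understatement in another.

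**Working it through.** **Inputs.** From Table 4: proportions 0.078, 0.047, 0.617 and 0.257, and L of 3, 6, 0.2 and 0.05 years. From the text before Table 4: overall prevalence 0.01. The article gives no formula for either disputed L, so there is no derivation to reproduce.

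**Weight of each category before utilities** (0.01 × proportion × L, years per admission):

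| Category | Calculation | Result |
|---|---|---|
| Death | 0.01 × 0.078 × 3 | 0.00234 |
| Permanent | 0.01 × 0.047 × 6 | 0.00282 |
| Moderate | 0.01 × 0.617 × 0.2 | 0.00123 |
| Minimal | 0.01 × 0.257 × 0.05 | 0.00013 |
| Sum | | 0.00652 |

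**Permanent disability.** 6 / 3 = 2.0, which is 100% longer. If the comment meant 3.5 to 4 years (assumption), the term falls from 0.00282 to 0.00165–0.00188, a cut of 33–42%. It would then drop below death as the largest term.

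**Moderate disability: lower limit.** Let a be the shortest duration possible in the 70% group. Then mean ≥ 0.70 × a + 0.30 × 0.5.

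- a = 0 (the comment alone): 0.150 years.
- a = 0.05 (the minimal-effect mean used as a floor): 0.185 years.
- a = 1/12 (one month, as in the six-category class "Moderate impairment, recovery 1–6 months"): 0.208 years.

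The entry of 0.2 is above the first two limits and equals the third at the table's precision.

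**Moderate disability: what 0.2 requires.** If every long case ended at just 6 months, the other 70% would have to average (0.2 − 0.15) / 0.70 = 0.071 years, about 26 days. If the long cases average more than 0.2 / 0.3 = 0.667 years (8 months), 0.2 cannot be reached even if every other case recovers at once.

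**Moderate disability: illustrative means (assumed shapes).**

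- 70% at 3.5 months, 30% at exactly 6 months: 0.7 × 3.5/12 + 0.3 × 0.5 = 0.354.
- Exponential with 70% resolved by 6 months: 0.5 / (−ln 0.3) = 0.415.
- 70% at 3.5 months, 30% at 9 months: 0.7 × 3.5/12 + 0.3 × 0.75 = 0.429.

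**Effect on total QALYs.** The non-fatal utilities are still to be determined, so I assume losses of 1 (death), 0.3–0.4 (permanent), 0.2–0.3 (moderate) and 0.05 (minimal), with equal RR. With 0.3 and 0.3, the base per preventable event at RR = 1 is 0.234 + 0.0846 + 0.0370 + 0.0006 = 0.3563.

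- Permanent at 4 years: 0.047 × 2 × 0.3 = 0.0282 lower, −7.9%. Over all combinations with 3.5–4 years: −8% to −13%.
- Moderate at 0.42 years: 0.617 × 0.22 × 0.3 = 0.0407 higher, +11.4%. Over all combinations at 0.42: +7% to +11%.
- Both changes: −5% to +4%.

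**If RR differs by category (assumed values).**

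- RR 0.1 for death and permanent, 0.3 for moderate and minimal; losses 0.3 and 0.3; L of 4 and 0.42. Before: 0.0234 + 0.00846 + 0.01111 + 0.00019 = 0.0432. After: 0.0234 + 0.00564 + 0.02332 + 0.00019 = 0.0526. Net +22%.
- RR 0.3 for death and permanent, 0.1 for the others; losses 0.4 and 0.2; L of 3.5 and 0.42. Before: 0.0702 + 0.03384 + 0.00247 + 0.00006 = 0.1066. After: 0.0702 + 0.01974 + 0.00518 + 0.00006 = 0.0952. Net −11%.

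**The case against.** A reader might infer that 0.2 years for moderate disability is arithmetically impossible, because a one-month floor gives a minimum of 0.208. The document does not support that. The comment alone permits 0.15 years. The one-month floor belongs to the two six-category systems in Table 3, and the adopted four-category system states no minimum duration. Row alignment in Table 3 does not make the classes equivalent: moderate events are 0.617 of the total in the adopted system, against 0.028 + 0.137 = 0.165 and 0.10 + 0.30 = 0.40 in the others. The adopted class may therefore include events that the others call minimal. Even with the floor, 0.208 rounds to 0.2 in a table that gives each L to one significant figure. This objection stands, and what remains is a question of plausibility.

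On permanent disability, one can say that the comment openly states an assumption, that its wording sets no numerical limit, and that no stated calculation fails to reproduce. That also stands: the document does not show whether the figure or the wording is wrong. It does not remove the conflict, because the comment is the only basis given for the 6.

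On size, all percentages rest on assumed utility losses, and the two changes pull in opposite directions. Moderate disability is 62% of events but only about 7–10% of QALYs under those losses.

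**Conclusion.** The permanent-disability entry contradicts its own rationale: 6 years is twice the figure it is said to exceed slightly, in the term with the largest weight before utilities. The moderate-disability entry is attainable but sits near the lower limit of its comment, at roughly half of what ordinary duration shapes give. Its derivation needs to be shown.

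Under the assumed losses, each change alone moves total QALYs by roughly 7–13%, downward for permanent and upward for moderate. The net effect is about −5% to +4% with equal RR. It can be larger when RR differs, at +22% and −11% in the two examples. The contradiction in wording rests on no assumption. The sizes depend on the assumed 3.5–4 years, the duration shape behind 0.42 years, the utility losses and the RR pattern. The point should be fixed before the model is populated, but it does not undermine the design.

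**What to change.** Three changes:

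1. Reconcile the permanent-disability entry with its comment, either with a value modestly above 3 years or with a stated justification for 6.
2. Recompute the moderate-disability mean from the duration distribution in the cited source and show the calculation. The 0.35–0.43 years above are illustrations and should not be adopted as replacements.
3. Vary L in the sensitivity analysis, for example permanent disability over 3.5–6 years and moderate disability over 0.2–0.43 years. Report each effect separately and the net effect on QALYs and on the ICER, using the elicited RR of each category.

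The cost is up to two table entries with their comments and a few extra model runs. No new data collection or elicitation is needed.
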